**Methods/Design:**

Starting on 1 April 2013, all consecutive immune-competent adult patients (>18 years old) admitted to a hospital ward with a positive febrile respiratory illness screening questionnaire and a diagnosis of pneumonia by the attending physician will be eligible for inclusion in this non-randomized study. All eligible patients who fulfill the ASP review criteria will undergo a prospective chart audit, followed by an ASP recommendation provided to the attending physician. The attending physician is responsible for implementing or rejecting the ASP recommendation. This is a modified stepped-wedge design with a baseline data collection period of 3 months, followed by non-random sequential introduction of the ASP intervention on each of four hospital wards in a single community-based, academic-affiliated 339-bed acute-care hospital in Barrie, ON, Canada. The primary outcome measure is hospital length of stay; secondary outcome measures include days and duration of antibiotic therapy, and inadvertent adverse outcomes of 30 day post-discharge mortality and hospital readmission rates. Differences in outcome measures will be assessed using extended Cox regression analysis. Time to ASP intervention is included as a time-dependent covariate in the final model, to account for time-dependent bias.

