### Intervention

All eligible patients with CAP who meet the ASP review criteria will receive the ASP intervention (ASP-i). This intervention consists of a prospective chart audit and physician feedback (persuasive) approach [25]. The ASP members who conduct all the audits and make recommendations consist of a pharmacist trained in infectious diseases (LM) and a physician trained in infectious diseases (GD). All patients are reviewed by both members. The ASP-i recommendations are guided by the Infectious Diseases Society of America CAP guidelines [1] and the Canadian Thoracic Society guidelines for the management of chronic obstructive pulmonary disease [26]. The possible ASP-i recommendations are based on those recommended by the UK National Health Service [25] and include:No change to current careDiscontinue antibioticsIntravenous to oral conversionDuration of therapyDosing changeNarrow or broaden spectrum of therapy.

The ASP-i recommendations are not mutually exclusive. All recommendations are documented in the patient’s electronic medical record and communicated directly to the attending physician by the ASP members.

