### Participant timeline

Enrollment of patients started 1 April 2013. The study is expected to enroll patients until 31 March 2015. All consecutive patients who meet the inclusion criteria and have no exclusion criteria will be eligible for the intervention. The ASP-i intervention may be implemented any time from 48 hours after admission in those patients who meet the criteria for ASP review. All patients who have not experienced an outcome measure at 14 days after admission will be censored from the study. Patients who die or are transferred from the ward (to the intensive care unit or other hospital) will also be censored. Patients who are discharged from hospital and are not censored will be contacted 30 days after discharge to determine their adherence with antibiotic prescription (if relevant), survival status, and readmission status.

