### Statistical methods

An extended Cox regression analysis that models the ASP-i as a time-variant covariate will be used to compare the primary and secondary outcome measures between the control and intervention groups [34]. Violations of the proportional hazards assumption for each covariate will be identified using the method of Schoenfeld residuals combined with the graphical method of log-log survival curve analysis [34]. Results will be reported as hazard ratios with 95 % confidence intervals. Patients who remain in hospital beyond 14 days will be administratively censored. Competing events, such as death or transfer from a medical ward to a critical care unit will be assumed to be non-informative conditional on the covariates included in the final model [34]. Time to ASP-i will be modeled as a time-variant covariate in the final model to account for any time-dependent bias [23]. The ASP-i exposure will be coded as a dichotomous variable; 0 = no ASP-i, switching to 1 = ASP-i at the time of the ASP-i and remaining 1 throughout the remainder of the follow-up time. This method treats a patient who has received an ASP-i as a non-ASP-i patient prior to the intervention. Other variables known to be associated with the primary and secondary outcome measures will also be included in the final model [5], and include; age, sex, Charlson comorbidity index, CURB-65 score, time (days) to clinical resolution, and complications from pneumonia, such as empyema. Fixed effects of wards on the outcomes will accounted for by including them as indicator variables in the final model. Maturation of ASP-i effect on outcomes over time will be adjusted by including a categorical time variable in the final model (time variable will be defined as ‘quarter’ from start of study). A dichotomous variable for acceptance or rejection of the ASP-i will be part of an interaction term with the control/intervention group variable to permit a per-protocol analysis. Sensitivity analysis will be done using a competing events Cox regression model to determine the impact of the assumption of the non-informative nature of events, such as death and admission to an intensive care unit [35].

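### The planned acceptance-by-group interaction is not a true interaction, and the estimable version should not be reported as a per-protocol effect

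*Protocol article*

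**What the plan says.** All references are to the Protocol article.

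- **Statistical methods, the term and its purpose.** "A dichotomous variable for acceptance or rejection of the ASP-i will be part of an interaction term with the control/intervention group variable", and this is "to permit a per-protocol analysis".
- **Statistical methods, the exposure.** The ASP-i is coded "0 = no ASP-i, switching to 1 = ASP-i at the time of the ASP-i and remaining 1 throughout the remainder of the follow-up time".
- **Abstract, Methods/Design.** "The attending physician is responsible for implementing or rejecting the ASP recommendation".
- **Participant timeline.** "The ASP-i intervention may be implemented any time from 48 hours after admission in those patients who meet the criteria for ASP review".
- **Intervention.** The list of possible recommendations runs from leaving care unchanged, through stopping antibiotics and switching from intravenous to oral treatment, to changes of dose, duration or spectrum. "The ASP-i recommendations are not mutually exclusive".
- **Statistical methods, patient-level adjustment.** The listed covariates are "age, sex, Charlson comorbidity index, CURB-65 score, time (days) to clinical resolution, and complications from pneumonia, such as empyema". Ward indicators and calendar quarter are added.
- **Blinding.** Attending physicians cannot be blinded to the ASP-i.

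**The concern.** An interaction between acceptance and group asks whether the effect of acceptance differs between control and intervention patients. That question needs acceptance to vary in both groups. Here it exists only once a recommendation has been made, so no control patient, and no intervention patient before review, can have accepted or rejected anything.

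The second difficulty is interpretation. Whether advice is accepted is decided after exposure, by a physician who knows the patient's progress. Several of the options, such as stopping antibiotics or going to oral treatment, are plausibly easier to accept in a patient who is recovering, and recovering patients also go home sooner. A result labelled per-protocol would be read as the effect on length of stay of following stewardship advice, when part or all of it could reflect which patients had the advice accepted.

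**Working it through.** **1. The plan's own figure.** The article gives no figure for the acceptance analysis. Its only effect size is in Sample size: about a 20 % reduction in length of stay, with power 0.80, two-sided alpha 0.05, 70 % discharged alive, and 400 to 500 patients a year for 24 months (800 to 1000 in total). With the Schoenfeld formula and an assumed 1:1 split of exposure:

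minimum detectable log HR = (1.960 + 0.842) / √(events × 0.5 × 0.5)

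For N = 900, events = 900 × 0.70 = 630, so log HR = 2.802 / √157.5 = 0.223 and HR = 1.25 (inverse 0.80). Over N = 800 to 1000 the HR runs from 1.27 to 1.24. The stated figure reproduces if it is read as an HR of 0.80 or its inverse, and it serves below as a yardstick.

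**2. Which states can occur.** Let G be the ASP-i indicator and A acceptance, with A coded 0 when there is no ASP-i.

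| State | G | A | G×A |
|---|---|---|---|
| No ASP-i (controls, and time before review) | 0 | 0 | 0 |
| ASP-i, rejected | 1 | 0 | 0 |
| ASP-i, accepted | 1 | 1 | 1 |

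The A and G×A columns are identical. The three columns have rank 2, so the interaction is exactly aliased with the acceptance main effect. More patients do not help, because the missing state (no ASP-i, yet accepted) cannot arise.

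**3. If A is coded missing without an ASP-i.** A complete-case fit discards every row with G = 0. G is then constant and only accepted versus rejected remains.

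**4. Group plus product only.** The columns G and G×A have full rank. With coefficients b1 and b2:

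- rejected versus no ASP-i: b1
- accepted versus rejected: b2
- accepted versus no ASP-i: b1 + b2

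This is the same model as a three-level exposure (none, rejected, accepted).

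**5. What selective acceptance could do to those contrasts.** The documents give no acceptance rate and no link between acceptance and clinical course, so this step is illustrative. Assumptions: N = 900; half of the patients due an ASP-i, given at day 2 if still in hospital; censoring at day 14; no true effect of the ASP-i or of acceptance; about 70 % acceptance; log-odds of acceptance rising by 1.0 per SD of a latent stability score; 40 replicates per setting. Discharge by day 14 was 86 to 89 % in these runs, above the plan's 70 %.

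| Effect of stability on discharge hazard, per SD | Rejected vs none | Accepted vs rejected | Accepted vs none |
|---|---|---|---|
| None | 1.01 | 0.97 | 0.98 |
| exp(0.25) | 0.86 | 1.24 | 1.07 |
| exp(0.5) | 0.78 | 1.43 | 1.12 |

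When stability itself was added to the model, all contrasts lay between 0.96 and 1.03. Departures of up to about 4 % are therefore within the noise of 40 replicates. The accepted-versus-rejected HR of 1.24 is about as large as the effect the trial is sized to detect (1.25 in step 1).

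**6. Whether the listed covariates measure stability when it matters.** CURB-65 is a severity score, and the article does not describe it as measured at the time of the recommendation. Time to clinical resolution is closest to clinical course. It is known only after baseline, may lie on the path from the intervention to discharge, and is likewise not described as status when the advice was given. The same holds for complications.

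**The case against.** The strongest defence is that the article never lists an acceptance main effect. Read as group plus product, the model is estimable and keeps the controls. It also yields accepted versus no ASP-i, the contrast a per-protocol analysis would want. Even with a main effect listed, dropping the duplicate column leaves the same fit. This stands: a reader might infer that the analysis cannot be run, or that only accepted versus rejected survives, and the documents support neither.

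A reader might also infer that controls will be dropped. The article does not say how acceptance is coded for them. That detail, like the rule for scoring several recommendations in one patient, may sit in the data dictionary or the analysis plan, so its absence is not held against the article.

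Thirdly, a reader might take it as shown that stable patients are those whose advice is accepted. The documents do not say this, and the model does adjust for CURB-65, time to resolution and complications. The simulated distortion disappears when stability is fully adjusted for. What this leaves is a possibility that the planned covariates are not designed to exclude, with no documented size.

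Finally, this is a secondary analysis. The main exposure is coded by receipt of the ASP-i, regardless of acceptance.

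**Conclusion.** The concern holds in a limited form. It is certain, and independent of sample size, that a genuine acceptance-by-group interaction cannot be identified: acceptance is undefined without an ASP-i, and the product duplicates the acceptance main effect. It is also clear from the article that the estimable version rests on a non-random choice made after exposure by an unblinded physician, and that no listed covariate is described as clinical status at the time of the recommendation. The result therefore should not be presented as the per-protocol effect of following stewardship advice.

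The direction and size of any bias are not established. The simulated hazard ratios (accepted versus none 1.07 to 1.12, rejected versus none 0.86 to 0.78) depend wholly on the assumed link between stability, acceptance and discharge. They show only that a visible difference can arise with no true effect. The primary extended Cox comparison is not touched by this point.

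**What to change.** 1. Replace the interaction by one three-level time-varying exposure: none, rejected, accepted. Make no ASP-i the reference, so that control time and time before review stay in the fit.
2. Drop the per-protocol label. Report the accepted and rejected contrasts as exploratory and non-causal.
3. Report the proportion accepted by recommendation type, since one patient may receive several. Show advice to leave care unchanged separately, because it asks for no action.

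Ward roll-out is not a ready substitute as an instrument for accepted advice. Ward order is non-random (Assignment of intervention), and the Discussion itself calls the contamination risk significant because hospitalists work across all wards.

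The cost is analysis wording only, with no new patients or change of conduct. The price is a weaker statement: the secondary analysis will describe what happened where advice was accepted or rejected, and will not estimate what following it achieves.

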### Monitoring

The hospital administration requires quarterly reporting of primary and secondary outcome variables. Secondary adverse outcome measures such as mortality and readmission rates to hospital within 30 days after discharge will be monitored in real-time by preprogrammed calculation of relative risk ratios adjusted by the LACE score [36]. Relative risk ratios >1.2 for death or readmission at 30 days post-hospital discharge for the intervention group will be used to notify the hospital administration that an inadvertent adverse event might be due to the intervention, and an external safety monitoring committee of the Hospital Pharmacy and Therapeutics committee will be responsible for auditing the program. This relative risk ratio was chosen by the hospital administration as a reporting trigger.

### Research ethics

The study has received approval from the research ethics board of the Royal Victoria Regional Health Centre (in an unnumbered research ethics board document entitled ‘*Intervention study of the impact of an antimicrobial stewardship program (ASP) on the length of stay of patients admitted to Royal Victoria Regional Health Centre with a diagnosis of community-acquired pneumonia (CAP) using a before-and-after quasi-experimental study with a control group’.*) A waiver of informed consent was approved by the research ethics board because of the nature of the pragmatic clinical trial [37, 38], based on the minimal risk of harm to patients and the fact that any ASP recommendation that is implemented will have required that the attending physician receive informed consent from the patient as per the usual process of care. A waiver for informed consent was also granted to the ASP members to contact the patients by phone 30 days after discharge, in order to ensure the safety of the program with respect to its impact on readmission and mortality rates. Any protocol amendments or violations will be reported to the research ethics board for review.

## Discussion

Pragmatic clinical trials are designed to embed research into practice, to reduce the delay observed in translating clinical research into practice [39]. Pragmatic clinical trials not only produce results that are immediately relevant to patients and stakeholders, but these results emerge from methodologically reliable designs [40]. Despite these qualities, pragmatic clinical trials made up only 2 % of registered clinical trials in ClinicalTrials.gov in the calendar year 2013 (search terms: ‘pragmatic* or practical* or comparative-effective*’ versus ‘clinical trials’ (accessed July 6, 2014)). In Canada, peer-reviewed research funding agencies dispensed over 45,500 grants and awards totalling more than $12 billion from 1999/2000 to 2013/2014, but only 480 of these totalling $118 million were used to support pragmatic clinical trials (Canadian Research Information System, http://webapps.cihr-irsc.gc.ca/cris/search; search terms: ‘pragmatic, practical, comparative-effectiveness’ (accessed July 6, 2014)). None of these grants and awards were used to support community-based pragmatic clinical trials. While this trial is designed to demonstrate the effectiveness of an ASP-i designed to reduce the length of hospital stay of CAP patients, an important finding that has yet to be published, it is also meant to demonstrate both the feasibility and value of research that is conceived and conducted by community-based healthcare providers. Given that more than 60 % of all inpatients in Ontario are admitted to community-based hospitals [41], it is essential that community-based healthcare providers are invited to suggest locally relevant research studies that are eligible for dedicated peer-reviewed funding opportunities. This study is intended to be an example and guide for those community-based healthcare providers interested in contributing to improving their healthcare programs and systems by using pragmatic clinical trial designs.

There are no previous studies examining the effectiveness of a prospective audit and feedback ASP-i on important patient outcomes that account for time-dependent bias. In general, these ASP-interventions are time-dependent interventions that have been incorrectly included as time-invariant covariates in statistical models. From an epidemiological perspective, these ASP-interventions are not present at the time of hospital admission but are ‘acquired’ at some time after admission to hospital. In the biased analysis, patients who are exposed to an ASP-i are analyzed as though the ASP-i had occurred at the time of hospital admission, thereby increasing the denominator of the length-of-stay hazard. The result of this mis-specification is a reduction in the length-of-stay hazard in the ASP-i group. The resultant length-of-stay hazard ratio will be biased and closer to 1, suggesting the absence of any beneficial ASP-i effect [23]. This study is the first to account for time-dependent bias by including ASP-i as a time-variant covariate in the final statistical model.

This study has several challenges to its internal and external validity. First, the absence of medical ward randomization could introduce selection bias. However, the allocation of patients to the ward and their medical provider is determined through a ‘natural’ allocation process that is blinded to the study, thus minimizing this potential source of bias. Secondly, the ASP members are not blinded to the intervention, outcome measure assessment, or data analysis. However, the likelihood of introducing bias is minimal because the primary and secondary outcome measures are stringently defined and objective. Thirdly, the risk of contamination is significant given that the hospitalists provide coverage across the four medical wards. It is conceivable that their behaviour will change over time as they become conditioned to the ASP-i and that this behaviour change might then precede the ASP-i as the study evolves over the 2 year period. The consequence of this contamination would be to bias the outcome hazard ratios toward a value of 1 or no ASP-i effect. However, a recent Cochrane review of the impact of audit and feedback on physician behaviour demonstrated only a 4.3 % (interquartile range, 0.5 % to 16 %) absolute increase in adherence with best practice [42], suggesting that the risk of contamination in this study might be small given the inherent resistance of physicians to changes in behaviour. In addition, the rate of ASP-i consults per month (defined as the ratio of the number of ASP-i consults to the number of eligible patients) will be modeled as time series data, and an assessment using regression analysis and the Durbin alternative test will be used to detect any serial correlation between the previous months’ ASP-i and the subsequent rate of ASP-i consults. Evidence of serial correlation between preceding ASP-i and subsequent rates of ASP-i consults would suggest possible contamination. Of course, contamination in this study might simply represent that the ASP was able to effectively change physician behaviour in a positive manner; a desirable impact for patient care, albeit with some undesirable effects on exposure-outcome evaluation. Fourth, the timing of the ASP-i at ≥48 hours after admission restricts the option of recommending earlier conversions from intravenous to oral antibiotics in eligible patients. Previous studies have suggested that earlier conversions might reduce length of stay [31, 43]. If the causal mechanism for reducing length of stay is through this earlier conversion, then this study might not be able to detect this ASP-i effect. As a single hospital site study, the applicability of the results to other hospitals and programs is unknown. However, a multi-site study using the same design, intervention, and analysis is currently being planned. Submissions of the proposal have been made to each participating hospital’s research ethics board. The anticipated start date of this multi-site study is 1 May 2015.

We believe that the ASP-i will lead to shorter lengths of hospital stay for CAP patients and reduced administration of unnecessary antibiotics, both of which should result in reduced rates of hospital-acquired complications and reduced healthcare costs. In addition, this study offers a model for community-based healthcare providers to design and conduct a pragmatic clinical trial for the purpose of programmatic evaluation. By involving community-based hospitalized patients and their healthcare providers in translating research into practice, access to improvements in our healthcare system will finally be more equitably distributed and shared.

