### Study design

This is a pragmatic controlled non-randomized clinical study intended to measure the effectiveness of a ‘real-world’ program [27]. The ASP-i will be implemented in a modified stepped-wedge design [28]. Baseline patient data will be collected for all enrolled patients on each of the medical wards for the first 3 months of the study, and then the ASP-i will be introduced to each medical ward in a non-randomized sequential fashion in 2-month intervals until all medical wards are exposed to the intervention. This design was chosen for several reasons; the preponderance of evidence suggests that antimicrobial stewardship interventions are beneficial to patient safety and quality of care [29]; there are human resource limitations in rolling out the program simultaneously to all wards; and the design has the advantage of a contemporaneous control group for comparison. The unit of randomization in this study could have been the four medical wards; however, randomization of the wards was not included in the design. The allocation of CAP patients to one of the four medical wards is controlled by bed allocation, an administrative branch of the hospital. Bed allocation was blinded to the study and the process of patient allocation is solely dependent on bed availability. In addition, the patients, regardless of their ward location, were all admitted to the hospitalist service. The hospitalist service provides coverage across all four medical wards and has no influence on the allocation of patients to any of the wards. In essence, the patients will be ‘naturally’ allocated to one of the four medical wards and one of the attending hospitalists by a bed allocation process that is blinded to the intervention, so that the additional randomization of the wards themselves should provide very little benefit with respect to minimizing selection bias. In addition, the four medical wards can all accommodate patients with CAP; however, one of the medical wards has historically accommodated more CAP patients than the other three. As a result, this ward was chosen as the first ward to receive the ASP-I, as this would ensure that the maximum number of CAP patients would have earlier access to the ASP-i. The ethical principle of utilitarianism was used to guide the order of ward exposure to the ASP-i. The target of the intervention is the most attending physician (hospitalist) , while the unit of analysis will be individual patient outcomes adjusted for potential clustering effects within hospital wards.

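### The contamination check reads serial correlation in the monthly consult rate as possible contamination, but the ward-by-ward roll-out puts serial correlation into that rate by design

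*Protocol article*

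**What the plan says.** The Discussion of the protocol article calls the contamination risk significant because hospitalists work on all four wards and may begin to act ahead of the ASP-i. It then sets out an empirical check. The series is the monthly rate of ASP-i consults, "defined as the ratio of the number of ASP-i consults to the number of eligible patients". The method is "an assessment using regression analysis and the Durbin alternative test will be used to detect any serial correlation" between earlier ASP-i and later consult rates. The stated reading is that "Evidence of serial correlation between preceding ASP-i and subsequent rates of ASP-i consults would suggest possible contamination".

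Three other statements fix the shape of that series:

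- Participant timeline, on who is eligible: "All consecutive patients who meet the inclusion criteria and have no exclusion criteria will be eligible for the intervention". The Population section likewise sets no condition that the patient's ward has started.
- Study design, on the baseline: "Baseline patient data will be collected for all enrolled patients on each of the medical wards for the first 3 months of the study".
- Study design, on the roll-out: the ASP-i is then "introduced to each medical ward in a non-randomized sequential fashion in 2-month intervals until all medical wards are exposed to the intervention".

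No roll-out, ward or hospitalist term is named for the check. The categorical quarter variable under Statistical methods belongs to the outcome model.

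**The concern.** A series that is zero for three months, rises in steps and then stays level is serially correlated, whatever the physicians do. A rule that equates serial correlation with possible contamination therefore confuses the planned roll-out with the behaviour it is meant to detect.

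The check is also blind where carry-over would matter for the between-ward comparison. On a ward not yet exposed the consult count is zero by design, so a hospitalist who already prescribes differently there leaves no trace in the ratio.

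This is the only empirical check the article describes for a threat that it says pulls the hazard ratios toward 1. The same section announces a multi-site study with the same design and analysis, so the rule may be carried forward.

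**Working it through.** The plan gives no figure for this check, so there is none to reproduce. The question is how often the rule signals when nothing has happened.

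**Inputs from the article.** 24 monthly points; 400–500 patients a year, so 400/12 = 33.3 to 500/12 = 41.7 a month (midpoint 37.5); three months with no ward exposed; four wards in 2-month steps, taken as starting in months 4, 6, 8 and 10; the first ward is the largest.

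**Assumptions, not in the article.** Ward shares 40/25/20/15, with a range from equal shares to 60/20/10/10. Share q of eligible patients on an active ward who get a consult: 0.5, range 0.3–0.8. A constant q means no contamination.

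**Expected series.** Expected rate in month t = q × (sum of the shares of active wards). With 40/25/20/15 and q = 0.5:

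| Months | Active share | Expected rate |
|---|---|---|
| 1–3 | 0 | 0 |
| 4–5 | 0.40 | 0.200 |
| 6–7 | 0.65 | 0.325 |
| 8–9 | 0.85 | 0.425 |
| 10–24 | 1.00 | 0.500 |

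The mean is (2×0.200 + 2×0.325 + 2×0.425 + 15×0.500)/24 = 9.4/24 = 0.392. Lag-1 autocorrelation = Σ(x_t − mean)(x_{t−1} − mean) / Σ(x_t − mean)² = 0.603/0.721 = 0.84. It does not depend on q, which only rescales the series.

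**Simulation without contamination.** Poisson ward counts, binomial consults with constant q, 2,000 runs per setting. The Durbin alternative test regresses the residual on the regressors and the previous residual, and tests the latter's coefficient against chi-square on 1 degree of freedom at 5%.

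| Specification | False signal, central case | Over the assumed ranges |
|---|---|---|
| Durbin test, constant only | 100% | 91–100% |
| Durbin test, linear month | 83% | 35–100% |
| Coefficient of previous month's consult count | 100% | 88–100% |
| Durbin test after previous month's rate | 62% | 49–63% |
| Durbin test after previous month's consult count | 24% | 11–27% |
| *Exposed share as regressor* | 7% | 5–8% |
| *Active-ward patients only as denominator* | 5% | 4–6% |
| *Months 10–24 only* | 6% | 4–6% |

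The Durbin test after the lagged count is sensitive to a small coding choice. The 11–27% sets the missing first residual to zero; dropping that month lowers the range to about 3–16%. Further runs of the active-ward version gave up to 10%, hence about 5–10% for the repaired check.

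**Does the check separate contamination from none?** If q drifts down over the trial by 25% or 50%, as pre-emptive good prescribing might cause, the constant-only test signals in 99.6% and 97.4% of runs, against 100% with no drift. The three repaired versions signal in 6–9% with the 25% drift and 16–40% with the 50% drift.

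**The case against.** The strongest defence is that the article does not fix enough for the check to be called wrong. The Intervention section says that eligible patients who meet the review criteria will receive the ASP-i, which can hold only on active wards. If the denominator carries that meaning, the false-signal rate is near nominal. The regressors and analysis window are also unstated and may be set in a fuller document; conditioning on the roll-out would largely remove the problem. Part of this stands: a reader might infer that the check signals in nearly every run whatever the model, and the table does not support that. But the written definitions do not tie eligibility to an active ward, and the objection is to a stated rule of interpretation, which does not mention the roll-out.

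The consult rate is also not irrelevant. Contamination in the article's sense includes behaviour that runs ahead of the ASP-i on active wards, and from month 10 no unexposed wards remain. There, fewer consults could reflect changed practice. That stands: the rate is a weak but relevant proxy on active wards and uninformative on the others.

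A reader might further infer that the check would be used to excuse a null hazard ratio. No section says so; the wording is only that contamination is possible. Nor does the absence of a hospitalist term show that the standard errors are wrong. The outcomes are to be "adjusted for potential clustering effects within hospital wards", but hospitalists treat both exposed and unexposed patients, and the article gives neither their number nor a within-physician correlation. That is a separate matter of undocumented size.

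**Conclusion.** The concern holds for the check as written. A hospital-wide consult rate under this roll-out is serially correlated by construction, so the stated reading does not follow. With no roll-out term, false signals occur in about 90–100% of simulated trials; with a linear trend, in about 35–100%; under some lagged specifications, far less often. These sizes rest on assumed ward shares, an assumed constant review share and month-4, 6, 8 and 10 starts. That the expected series rises from zero to a plateau needs only the roll-out and a denominator covering all wards.

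It would be too strong to conclude that the primary result is at risk. The check feeds no estimate, and the outcome model has its own ward and quarter terms. What is at stake is a diagnostic that cannot distinguish contamination from its absence and that does not see wards awaiting the intervention. This should be corrected before the check is interpreted or reused.

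**What to change.** 1. State the denominator as eligible patients on wards where the ASP-i is active that month. Alternatively, put the exposed share of eligible patients in the regression, or analyse months 10–24 only. Drop the reading that serial correlation in the hospital-wide rate suggests contamination. This costs a change of wording. The repaired check still has low power for modest drift, and the text should say so.

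2. Add a supportive check of carry-over: relate prescribing in the first 48 hours, before any ASP-i can act on that patient, to the attending hospitalist's number of prior ASP-i recommendations, adjusted for ward and calendar time. It needs the attending hospitalist to be recorded, which is assumed here, and an attribution rule for shared care. Power is limited because prior exposure tracks calendar time. Restricting it to wards not yet exposed in months 4–9 would leave few patients: 37.5 × 2 × (0.60 + 0.35 + 0.15) = 82.5 with 40/25/20/15 shares, or 37.5 × 2 × (0.75 + 0.50 + 0.25) = 112.5 with equal shares.

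3. Optionally, as a separate sensitivity analysis, fit the outcome model with a hospitalist shared frailty. The correction of the contamination check does not depend on it.
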